# Intraoperative wound irrigation to prevent surgical site infection after laparotomy (IOWISI): study protocol for a randomized controlled trial

**DOI:** 10.1186/s13063-017-2154-6

**Published:** 2017-09-04

**Keywords:** Surgical site infection, Abdominal surgery, Visceral surgery, Laparotomy, Intraoperative wound irrigation, Polyhexanide, Randomized controlled trial

## Abstract

**Background:**

Postoperative surgical site infection (SSI) is one of the most common hospital infections and contributes substantially to postoperative morbidity and mortality. In addition, SSIs dramatically increase the treatment cost and length of hospital stay. Following visceral surgery by laparotomy, SSI rates are especially high (14–25%). Therefore, measures to prevent SSI in this field are urgently needed. Prophylactic intraoperative wound irrigation (IOWI) of the subcutaneous soft tissue before skin closure hypothetically represents an easy and economical option to reduce SSI rates and is already frequently used in clinical practice. However, there are currently no definite recommendations on the use of IOWI since high-level evidence supporting its use is lacking. Consequently, clinical practice varies widely. Antiseptic polyhexanide (PHX)-based solutions are approved for soft-tissue wound irrigation in surgery but have not been specifically evaluated in randomized clinical trials for the prevention of SSI following laparotomy for visceral surgery.

**Methods/design:**

The IOWISI trial is a multicentre, randomized, observer- and patient-blinded clinical trial with three parallel treatment groups, comparing IOWI with a 0.04% PHX solution to no irrigation (test 1) or saline (test 2) before skin closure after laparotomy for visceral surgery (contamination level II–IV). The primary endpoint of the trial is the SSI rate within 30 days postoperatively. Statistical analysis of the primary endpoint measure will be based on the intention-to-treat population. The global level of significance is set at 2.5% for test 1 and 5% for test 2 and the sample size (*n* = 540) is determined to assure a power of 94% (test 1) and 85% (test 2).

**Discussion:**

The IOWISI trial will provide high-level evidence as a basis for clinical recommendations regarding the use of IOWI with PHX or saline and will potentially impact on future clinical guidelines and practice. The pragmatic trial design guarantees high external validity.

**Trial registration:**

Registered at the German Clinical Trials Register, DRKS00012251. Registered on 3 July 2017.

**Electronic supplementary material:**

The online version of this article (doi:10.1186/s13063-017-2154-6) contains supplementary material, which is available to authorized users.

## Background

### Rationale

Postoperative surgical site infection (SSI) is one of the most common hospital infections. SSI rates are especially high following visceral surgery by laparotomy. Depending on the level of intraoperative contamination, recent high-level randomized controlled trials (RCTs) with standardized SSI definitions report postoperative SSI rates between 14.5% and 25.0% [1–3]. Studies have shown an increase of 6–24 days in the mean length of hospital stay if SSI occurs [4]. In addition to the risk and discomfort for the patient, SSIs dramatically increase the cost of treatment. In Germany, postoperative SSIs account for approximately 1 million extra days of hospitalization and an additional cost of around € 3 billion per year [5]. Prophylactic intraoperative wound irrigation (IOWI) of the subcutaneous and deep soft tissue before skin closure with saline or antiseptic solutions hypothetically represents an easy and economical option to reduce SSI rates and is already frequently used in clinical practice [6, 7]. However, the latest official guidelines for the prevention of SSI by the Centres for Disease Control and Prevention (CDC) [8] and the World Health Organization (WHO) [9] conclude that IOWI with saline is not efficient and IOWI with diluted polyvinylpyrrolidone-iodine (PVP-I) solutions may have a potential benefit in preventing SSI. However, due to the low level of underlying evidence these recommendations are conditional [8, 9]. In contrast, the clinical guidelines of the British National Institute for Health and Clinical Excellence (NICE) from 2008 state that the efficacy of IOWI is unproven for any irrigation solution and that its use should be avoided to prevent potential tissue toxicity and systemic side effects of PVP-I and other antiseptics [10]. However, all of these recommendations are based on a small number of unstandardized and heterogeneous RCTs evaluating different types of surgery (abdominal, as well as orthopaedic and neurosurgical procedures) and different types and concentrations of irrigation solutions.

Antiseptic polyhexanide (PHX)-based solutions are approved for prophylactic intraoperative soft tissue wound irrigation and have been shown to be tissue tolerable without being resorbed [11, 12]. Therefore, side effects such as allergic reactions are extremely rare. PHX inhibits microbial attachment to wound surfaces through an interaction with the bacterial membrane. In vitro data show a superiority of PHX over PVP-I against a broad microbial spectrum, including multi-resistant strains [13]. However, there are no recommendations on IOWI with PHX in any of the current guidelines on SSI prevention [8–10].

### Previous trials

Even though the literature evaluating SSI prevention is substantial, high-level evidence to guide decisions on the use of IOWI with saline or antiseptics remains scarce. Our research group previously performed a large-scale meta-analysis of 41 RCTs on IOWI with saline, PVP-I, or antibiotic irrigation solutions, exclusively in abdominal surgery. The results of this analysis show a risk reduction of 46% in the treatment group (IOWI with any irrigation solution) [14]. The SSI incidence was 9% in the treatment group compared to 16% in the untreated group (*p* < 0.05). However, the majority of included trials were out of date (1970–1990) and most of them revealed a high risk of bias mainly because of insufficient data reporting or methodological flaws. In addition, interventions, follow-up times, and definitions of SSI varied widely between those trials. Furthermore, neither the WHO nor the NICE guidelines recommend the use of topical antibiotic solutions for this indication anymore [9, 10].

The only standardized RCT comparing IOWI with saline irrigation versus no irrigation after open appendectomies was published in 2000 and found a reduction of SSI from 25% to 8.7% in the saline irrigation group [15].

Recently, PHX-based antiseptic solutions have been successfully and widely used in orthopaedic and trauma surgery [11, 16]. In a longitudinal cohort study, irrigation of traumatic contaminated soft tissue wounds with PHX showed a reduction of the SSI rate of almost 75% compared to irrigation with Ringer’s solution [16, 17]. One pilot study investigated differences in SSI rates for “short” versus “long” IOWI with PHX 0.04% solution in abdominal surgery in 97 patients [18]. In the experimental group the subcutaneous tissue was irrigated through the aponeurosis prior to the initial incision and the wound margins were protected with PHX-soaked abdominal cloths during the whole procedure. After closing the abdominal fascia, wounds were again irrigated with PHX (“long”). In the retrospective control group, wounds were irrigated with PHX only before skin closure (“short”). No significant differences in SSI rates were observed between the two groups. The overall SSI rate in this single-centre study was comparable to observations of other recent trials (19.6%) [18]. This might be explained by the fact that wounds were subsequently rinsed with saline solution after PHX irrigation (see Discussion).

### Objective

The IOWISI trial aims to investigate if IOWI with PHX solution (0.04%) or saline (NaCl 0.9%) can reduce the rate of postoperative SSI within 30 days (according to the CDC definition [19]; Table 1) after laparotomy for visceral surgery. The results of the IOWISI trial will provide high-level evidence for future clinical recommendations regarding the use of IOWI in visceral surgery by laparotomy and provide the participating patients the opportunity of a potentially improved treatment.

**Table 1 Tab1:** Definition and classification of surgical site infection (SSI) [19]

Superficial incisional SSI	Infection occurs within 30 days after the operation and infection involves only skin or subcutaneous tissue of the incision and at least *one* of the following: • Purulent drainage, with or without laboratory confirmation, from the superficial incision. • Organisms isolated from an aseptically obtained culture of fluid or tissue from the superficial incision. • At least one of the following signs or symptoms of infection: pain or tenderness, localized swelling, redness, or heat *and* superficial incision is deliberately opened by surgeon, *unless* incision is culture-negative. • Diagnosis of superficial incisional SSI by the surgeon or attending physician. Notes: Do *not* report the following conditions as SSI: • Stitch abscess (minimal inflammation and discharge confined to the points of suture penetration).
Deep incisional SSI	Infection occurs within 30 days after the operation and the infection appears to be related to the operation and infection involves deep soft tissues (e.g. fascial and muscle layers) of the incision and at least *one* of the following: • Purulent drainage from the deep incision but not from the organ/space component of the surgical site. • A deep incision spontaneously dehisces or is deliberately opened by a surgeon when the patient has at least one of the following signs or symptoms: fever (>38 °C), localized pain, or tenderness, unless site is culture-negative. • An abscess or other evidence of infection involving the deep incision is found on direct examination, during reoperation, or by histopathologic or radiologic examination. • Diagnosis of a deep incisional SSI by a surgeon or attending physician. Notes: • Report infection that involves both superficial and deep incision sites as deep incisional SSI. • Report an organ/space SSI that drains through the incision as a deep incisional SSI.
Organ/space SSI	Infection occurs within 30 days after the operation and the infection appears to be related to the operation and infection involves any part of the anatomy (e.g. organs or spaces), other than the incision, which was opened or manipulated during an operation and at least *one* of the following: • Purulent drainage from a drain that is placed through a stab wound into the organ/space. • Organisms isolated from an aseptically obtained culture of fluid or tissue in the organ/space. • An abscess or other evidence of infection involving the organ/space that is found on direct examination, during reoperation, or by histopathologic or radiologic examination. • Diagnosis of an organ/space SSI by a surgeon or attending physician.

## Methods/design

### Trial sites

The IOWISI trial will be conducted in at least 10 surgical departments (university and community hospitals), all of which are members of the German surgical trial network (CHIR-*Net*) and have previously participated in multicentre trials. All of the study personnel involved in the trial require training according to the International Conference on Harmonisation of Technical Requirements for Registration of Pharmaceuticals for Human Use – Good Clinical Practice (ICH-GCP) and will be instructed in all trial-specific procedures before initiation of the trial, conforming to German Drug Law (*Arzneimittelgesetz* (AMG) [20]) and GCP regulations [21]. After training by the principal investigator, the leading surgeon of the operating team will perform the intervention.

### Trial population and eligibility criteria

All adult patients (≥18 years) scheduled for visceral surgery by midline or transverse laparotomy (elective and emergency) will be eligible if they are able to understand the extent and nature of the IOWISI trial and provide written informed consent to participate. Exclusion criteria were defined as: a) pregnant or breast-feeding women; (b) known hypersensitivity/allergy to PHX; (c) American Society of Anesthesiologists (ASA) score > 3; (d) critical medical condition of emergency patients precluding informed consent or sufficient time to reflect on the decision to participate in the trial; (e) inability to give/understand informed consent or to attend follow-up visits; (f) clean/Class I procedures according to the CDC classification (Table 2) or surgery without opening of the abdominal cavity; (g) laparoscopic surgery; (h) previous abdominal surgery within the last 30 days or planned re-laparotomy within the next 30 days; (i) patients with severe immunosuppression; (j) presence of concurrent abdominal wall infections; (k) preoperative systemic antibiotic therapy within 5 days prior to surgery (except emergency antibiotic treatment due to septic peritonitis after admission to the hospital; routine intraoperative antibiotic prophylaxis is allowed); (l) participation in another clinical trial that interferes with the primary or secondary outcomes of this trial.

**Table 2 Tab2:** Classification of wound contamination levels according to CDC [19]

Class I/clean	These are uninfected operative wounds in which no inflammation is encountered and the respiratory, alimentary, genital, or uninfected urinary tracts are not entered. In addition, clean wounds are primarily closed and, if necessary, drained with closed drainage. Operative incisional wounds that follow non-penetrating (blunt) trauma should be included in this category if they meet the criteria. Laparoscopic surgeries, surgeries involving the skin (such as biopsies), eye, or vascular surgeries are good examples.
Class II/clean-contaminated	An operative wound in which the respiratory, alimentary, genital, or urinary tracts are entered under controlled conditions and without unusual contamination. Specifically, operations involving the biliary tract, appendix, vagina, and oropharynx are included in this category, provided no evidence of infection or major break in technique is encountered.
Class III/contaminated	Open, fresh, accidental wounds. In addition, operations with major breaks in sterile technique (e.g. open cardiac massage) or gross spillage from the gastrointestinal tract, and incisions in which acute, non-purulent inflammation is encountered are included in this category. Contaminated wounds are also created when an outside object comes in contact with the wound (e.g. a bullet, knife blade, or other pointy object).
Class IV/dirty-infected	Old traumatic wounds with retained devitalized tissue and those that involve existing clinical infection or perforated viscera or a foreign object lodged in the wound or any wound that has been exposed to pus or faecal matter. This definition suggests that the organisms causing postoperative infection were present in the operative field before the operation.

*CDC* Centres for Disease Control and Prevention

### Sample size

For statistical significance 540 patients have to be recruited, 230 patients in the PHX and the saline group, respectively, and 80 patients in the control group (see Statistical methods).

### Type of trial

This is a randomized, controlled, observer- and patient-blinded, multicentre, surgical trial with three parallel study groups, phase IIIb according to German Drug Law (*AMG*).

### Recruitment and trial timeline

Only surgical departments with adequate patient numbers will be included in the trial to assure the target sample size. The recruitment period is set at 27 months (first patient in to last patient out, 28 months). Figure 1 shows the trial flow scheme and Fig. 2 (SPIRIT figure) shows the schedule of enrolment, interventions, and assessments according to the diagram of the SPIRIT 2013 statement [22]. The SPIRIT checklist for this study protocol can be found in Additional file 1.

**Fig. 1 Fig1:**
[figure not shown]
Flow chart of the IOWISI trial. *IOWI* intraoperative wound irrigation, *PHX* polyhexanide, *SSI* surgical site infection, *ITT* intention-to-treat

**Fig. 2 Fig2:**
[figure not shown]
SPIRIT figure for the IOWISI trial (according to SPIRIT 2013 [22]). *AE* adverse event, *ALAT* alanine aminotransferase, *ASAT* aspartate aminotransferase, *Cr* creatinine, *Glu* glucose, *IOWI* intraoperative wound irrigation, NNIS National Nosocomial Infection Surveillance, *PHX* polyhexanide, *POD* postoperative day, *SAE* serious adverse event, *SSI* surgical site infection, *ITT* intention-to-treat

### Randomization and blinding

Prior to inclusion in the trial, a GCP-certified investigator will perform the screening and collect detailed information from the patients and will obtain their written informed consent. An online tool of the Munich Centre of Clinical Trials (*Münchner Studien Zentrum* (MSZ)) will be used to generate the allocation sequence. This online tool uses pre-defined randomization lists, which will be created block-wise at the Institute of Medical Statistics and Epidemiology (*Technische Universität München* (TUM)) and will be stratified by study centre and level of contamination of the surgical procedure (class II–IV; Table 2).

A member of the study team will perform randomization during surgery after closure of the abdominal fascia is completed and will inform the surgical team of the assigned treatment. To assure balanced group sizes in the course of the accrual, a block-wise randomization is applied. Baseline characteristics of the patient and day of randomization must be documented on the printed randomization sheets. Subsequently, randomization sheets must be stored away from the patient records and trial documents to ensure blinding. The surgical team cannot be blinded, as no irrigation is used in the control group. However, patients, outcome assessors, and the trial statistician will be blinded for the trial intervention. The primary endpoint (SSI up to postoperative day 30) will be assessed clinically by a member of the local study team who will neither be part of the surgical team that performs the intervention nor have access to the randomization results in order to comply with observer-blinding. In addition, wound photographs will be taken at each study visit and evaluated via a central database by independent outcome assessors at spatially separated participating study sites. Unblinding of the local principal investigator is permissible if significant hazards for subjects’ safety or welfare occur.

### Interventions

#### Experimental interventions

Preoperative skin preparation, application of antibiotic prophylaxis, and the surgical procedure will be performed according to local standard procedures. After closure of the abdominal fascia, patients will be randomized to one of the following groups.

In the experimental group 1, the subcutaneous soft tissue will be irrigated with 1000 ml of a 0.04% PHX solution, which is the recommended concentration for surgical wound irrigation according to the medicinal product's professional information. The whole surface of the wound will be carefully rinsed with the irrigation solution and the excess fluid will be removed by suction. Debris and blood clots should be removed from the wound using irrigation/suction. The wound is not to be rubbed dry with abdominal cloths, but left moistened with the irrigation solution to ensure sufficient contact time for PHX to assure the desired antiseptic effect. After irrigation with PHX the wound will not be irrigated with saline again. Since PHX is a cation-active substance, it is not compatible with anionic organic substances (e.g. lactate). Furthermore, the combination of PHX with PVP-I products has to be avoided.

In the experimental group 2, the same intervention will be performed using 1000 ml of saline solution (NaCl 0.9%).

After irrigation of the wound, the skin closure and sterile dressing will be performed according to local standards, without any further wound-related procedure. PHX and saline solutions are to be purchased, stored, and distributed according to the respective standard operating procedures of the trial centres. If the operating surgeon decides that incomplete closure of the wound and/or any other wound-related procedure after the study intervention (e.g. negative pressure treatment) is necessary for the benefit of the patient, the patient will have to be excluded from the trial.

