#### Analysis population

The primary and secondary endpoints will be analysed on the intention-to-treat (ITT) set consisting of all patients randomized in the study independent of the intervention they receive (analysis ‘as randomized’). The safety analysis will be performed on the safety set consisting of all patients randomized into the study and assigned to the treatment group of their actual treatment.

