#### Sensitivity of the primary endpoint measure

A dropout rate of 8–10% is expected in this study based on experience from similar trials previously conducted in the CHIR-*Net* [1]. The primary endpoint analysis will be based on all patients with complete SSI follow-up. In order to examine the sensitivity of the results, multiple imputations will additionally be used to estimate missing primary endpoint data.

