### Withdrawals

Patients are free to withdraw from trial participation at their own request at any time and without giving reasons for their decisions. Withdrawals will be documented in the eCRF and in the patient’s medical record. However, all on-going SAEs must be followed up and documented until their final outcome can be determined. In addition, the investigator has the right to withdraw a patient from the study at any time. Reasons for withdrawal from the study may include but are not limited to the following: (a) any medical condition that the investigator or sponsor determines may jeopardize the patient’s safety if he or she continues in the study; (b) if it is discovered that a study subject is pregnant or may have been pregnant at the time of intervention. Patients who withdraw from the study will not be replaced.

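### The exclusion rule for non-standard wound closure lets an unblinded surgeon remove randomized patients, which conflicts with the ITT set and opens a risk of selection bias in the primary analysis

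*Protocol article*

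**What the plan says.** Four parts of the protocol article bear on this point.

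- **Randomization and blinding.** "A member of the study team will perform randomization during surgery after closure of the abdominal fascia is completed", and that person "will inform the surgical team of the assigned treatment". The article also states: "The surgical team cannot be blinded, as no irrigation is used in the control group".
- **Experimental interventions.** The rule applies when the operating surgeon opts to leave the wound partly open or to carry out "any other wound-related procedure after the study intervention (e.g. negative pressure treatment"). Where the surgeon judges that such a step "is necessary for the benefit of the patient, the patient will have to be excluded from the trial". The Control intervention section says only that wounds are not irrigated and contains no such rule.
- **Analysis population.** Primary and secondary endpoints are analysed on an ITT set "consisting of all patients randomized in the study independent of the intervention they receive". The safety set also starts from all randomized patients.
- **Sensitivity of the primary endpoint measure.** "The primary endpoint analysis will be based on all patients with complete SSI follow-up". Multiple imputation is added as a sensitivity analysis, and a dropout rate of 8-10% is expected.

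Nothing in the article says that a patient excluded under the closure rule continues to be followed. The Withdrawals section does not name this case among its examples, and it adds: "Patients who withdraw from the study will not be replaced".

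**The concern.** An ITT analysis protects the comparison because nothing that happens after allocation can change who is counted. The closure rule weakens that protection. Its trigger is a judgement about the wound, which is plausibly related to SSI risk, since contaminated and dirty wounds (classes III and IV) are eligible. The person judging knows whether, and with what, the wound was irrigated. If the judgement leans on that knowledge even slightly, the patients left in each arm are no longer comparable.

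Blinded outcome assessment does not help, because an excluded patient may never reach the assessor. Few events are expected (230 x 2.2% = about 5 SSIs in the PHX arm), so the result is sensitive to a handful of removals.

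**Working it through.** **1. What happens to an affected patient under the text as written.**

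| Step | Section | Consequence |
|---|---|---|
| Fascia closed, patient randomized, surgeon told the arm | Randomization and blinding | Patient belongs to the ITT set |
| Surgeon decides on incomplete closure or another wound procedure | Experimental interventions | Patient is excluded from the trial |
| All randomized patients are analysed | Analysis population | Patient should be counted |
| Primary analysis uses complete SSI follow-up | Sensitivity of the primary endpoint measure | An excluded patient without follow-up is not counted |

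Only the multiple-imputation sensitivity analysis could bring the patient back, and the article does not say that it covers these exclusions.

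**2. The plan's own power figures.** Inputs from Sample size calculation: SSI 2.2% (PHX), 8.7% (saline), 16.2% (control); 230/230/80 patients; two-sided Fisher exact test; alpha 2.5% for test 1 and 5% for test 2. Stated power is 94% and 85%. Full binomial enumeration gives:

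- two-sided p as twice the smaller tail: 94.9% and 85.4%;
- two-sided p by minimum likelihood: 96.5% and 85.4%.

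The stated figures are reproduced to within one point on the first definition.

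**3. Equal exclusion in all arms.** The exclusion rates here and below are assumptions, because the article gives none. With design SSI rates unchanged (doubled tail):

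- 5% excluded (218/218/76): power 93.8% and 83.1%;
- 10% excluded (207/207/72): power 92.3% and 80.7%.

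This is a modest loss of power and brings no bias between arms.

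**4. Exclusion in one arm only, with no true difference.** Assume SSI 8.7% in both PHX and saline, a fraction e excluded from one of them, and SSI risk r among those excluded. The rate seen in the depleted arm is

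q = (0.087 - e x r) / (1 - e).

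- e = 5%, r = 30%: (0.087 - 0.015)/0.95 = 7.6%
- e = 5%, r = 50%: (0.087 - 0.025)/0.95 = 6.5%
- e = 10%, r = 30%: (0.087 - 0.030)/0.90 = 6.3%
- e = 10%, r = 50%: (0.087 - 0.050)/0.90 = 4.1%

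Probability that test 2 rejects at 5%, with 230 patients in the intact arm:

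| Excluded in one arm | n in that arm | r | Doubled tail | Minimum likelihood |
|---|---|---|---|---|
| 0% | 230 | - | 3.5% | 3.5% |
| 5% | 218 | 30% | 5.1% | 5.9% |
| 5% | 218 | 50% | 10.4% | 12.1% |
| 10% | 207 | 30% | 11.2% | 13.6% |
| 10% | 207 | 50% | 42.4% | 46.3% |

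If 5% are excluded from both arms instead, test 2 rejects 3.2-3.3%, so the error rate is kept. The harm comes from exclusion that differs by arm.

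The last row is extreme: the excluded would carry 0.050/0.087 = 57% of that arm's SSIs. In the mildest one-arm case the share is 0.015/0.087 = 17%.

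**5. A case that hardly matters.** Suppose 6% of control and 2% of PHX patients are excluded, with 40% SSI risk. The rates become (0.162 - 0.024)/0.94 = 14.7% and (0.022 - 0.008)/0.98 = 1.4%. With 225 and 75 patients left, the probability that test 1 rejects moves only from 94.9% to 94.7% (doubled tail). The size of the problem therefore depends on the pattern of exclusion.

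**The case against.** Several points on the other side are fair.

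- **Timing.** The phrase about the study intervention dates the added procedure, not the surgeon's decision, and need not apply to incomplete closure. A surgeon could settle at fascial closure, before allocation, that the skin will stay open. This stands, so the claim is that the rule permits exclusion after randomization, not that every such exclusion falls there.
- **Meaning of exclusion.** The article does not define exclusion from the trial as removal from the analysis set. On one reading the Analysis population section governs and the patient merely has a missing outcome. That reading softens the contradiction but does not cure it: the primary analysis still leaves the patient out, and the missingness may be informative.
- **Selective removal.** A reader might infer that the rule does remove high-risk wounds selectively by arm, for instance dirty wounds that were not irrigated. The article does not support this. It gives no number, risk profile or direction for these exclusions, and the absence of the rule from the Control intervention section leaves open whether it applies there at all.
- **Frequency.** Such cases may be rare, and the inflation shown requires exclusion concentrated in one arm. Both points stand.

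That an analysis plan may exist elsewhere is no answer, because both conflicting rules are stated in this article.

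**Conclusion.** The point holds as a conflict within the plan. The closure rule permits removal of a randomized patient by a surgeon who knows the arm; the ITT definition keeps that patient; and the complete-follow-up rule drops the patient from the primary result. This opens a risk of selection bias in either direction. Whether bias would occur, and how large it would be, cannot be read from the document.

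The 5-12% and 11-46% rejection rates for test 2 rest on the assumed exclusion fractions, on exclusion in a single arm and on a 30-50% SSI risk among the excluded. Their ranges span two common definitions of the two-sided Fisher p-value. They show that the nominal 5% can be exceeded, not that it will be. The stated power figures are not in question.

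Correction is nonetheless warranted, because outcomes not collected on excluded patients generally cannot be recovered at the analysis.

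**What to change.** Reconcile the sections Experimental interventions, Control intervention, Analysis population and Sensitivity of the primary endpoint measure so that one rule applies to all three arms. A randomized patient with non-standard closure or an added wound procedure:

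- stays in the randomized arm;
- is followed to day 30 for SSI;
- is counted in the primary ITT analysis;
- has the procedure recorded as a deviation.

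Any analysis that omits such patients should be a sensitivity analysis only. The Withdrawals section should be worded consistently with this. The clinical decision on the wound stays with the surgeon.

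Optionally, record on the existing randomization sheet, before allocation, whether primary skin closure is intended. Patients not meant for closure could then be identified before they are randomized.

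**Cost.** A few sentences across these sections, continued follow-up of a few patients and, if adopted, one extra item on the sheet. The planned 540 patients and the stated power do not change. The downside is that a few patients with non-standard closure remain in the primary analysis. For them, one superficial SSI criterion in Table 1 (deliberate opening of the incision) fits an open wound poorly, although the others, such as purulent drainage, culture or physician diagnosis, still apply.
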